### Randomization and patient allocation

The web-based Research Management database system (ResMan; www.medresman.org) will be used to allocate patients in a 1:1:1:1 ratio. The data coordinating center (DCC) statisticians will generate and validate the randomization scheme for the study before it is implemented in the ResMan database system. When a participant is enrolled, an investigator at the participating site will take out a sealed envelope and enter the identification number into the ResMan database system and will log in to a password-protected secured website designed by the DCC to determine the group allocation.

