### Sample size calculations

In previous studies, the overall live birth rate for infertile women with PCOS who received letrozole for 6 months was 36.3% [28], whereas for women who received fixed acupuncture twice per week with a maximum of 32 acupuncture treatments, the overall live birth rate was 13.9% [10]. Thus, we hypothesize that the live birth rate is 35% for four cycles of letrozole treatments and 15% for fixed acupuncture three times per week. We have chosen 10% as the minimal clinically detectable difference that is likely to change clinical practice. Assuming a 35% live birth rate with letrozole, a 25% live birth rate with personalized acupuncture, a 15% live birth rate with fixed acupuncture, a 5% live birth rate with placebo letrozole, and an 80% power at a significance level of 0.05, we calculated that 250 subjects per treatment group were required. The sample size was increased from 250 to 275 per group considering a 10% dropout rate, and thus 1100 women in total will be enrolled.

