The analysis of secondary (supplemental) outcomes measured over time will entail the application of statistical methods that have been developed for correlated data because repeated observations will be made over time for each individual. For secondary outcomes such as hormone levels, a linear mixed-effect model will be fit where the main independent variables will be treatment group, time, and their interaction as well as the designed randomization stratification factors as covariates. Logistic regression models will be used in secondary analyses to evaluate the predictive value of treatment arm, clinical site, body mass index, and other explanatory variables on binary outcomes (e.g., live birth, abortion). Cox proportional hazards models and the Kaplan-Meier method will be used to compare time to pregnancy in the treatment groups. Effects on QOL, as determined by the change from baseline physical and mental component scores, will be analyzed by univariate and multivariate ANCOVA. The adequacy of blinding will be tested by Fisher’s exact test comparing true group assignments with participant guesses, including “don’t know.” In order to evaluate acupuncture as a unique therapy, the combination of the personalized acupuncture group and fixed acupuncture group will also be compared with the combination of the letrozole and placebo letrozole groups for the analysis of primary outcome. Differences in AE rates will be analyzed in a negative binomial generalized linear model. A *P* value < 0.05 with a two-tailed test will be considered significant. All statistical analyses will be performed using IBM SPSS Statistics version 21.0 software (IBM Corp., Armonk, NY, USA).

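### The 10% dropout allowance is 250 × 1.10 = 275 per group, which covers only 9.1% loss; covering 10% takes 278, a minor slip to correct in wording while keeping 1100 women

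*Protocol article*

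**What the plan says.** All the figures are in the Sample size calculations section of the protocol article. The assumed live birth rates are given as "Assuming a 35% live birth rate with letrozole, a 25% live birth rate with personalized acupuncture" and "a 15% live birth rate with fixed acupuncture, a 5% live birth rate with placebo letrozole", so neighbouring groups differ by 10 percentage points. That is the difference the plan wants to detect: "We have chosen 10% as the minimal clinically detectable difference". With "an 80% power at a significance level of 0.05", the section says "we calculated that 250 subjects per treatment group were required". The allowance for loss follows: "The sample size was increased from 250 to 275 per group considering a 10% dropout rate", which gives 1100 women in total.

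Two other sections bear on what the allowance means. Data analysis specifies an intention-to-treat primary analysis with a Pearson chi-square test. Imputation procedure for missing data describes dropouts as essentially women who withdraw consent for further follow-up, and says that they will be kept in the analysis by imputation.

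**The concern.** A dropout rate is a fraction of the women enrolled. If 250 per group are needed after 10% have been lost, the number enrolled must satisfy N × 0.90 ≥ 250. The plan instead adds 10% of the 250, so the enrolled number falls slightly short of what the same paragraph requires under its own dropout rate. At stake is whether the published justification agrees with itself, and whether a reader who later compares planned with achieved numbers has a correct benchmark.

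**Working it through.** **Inputs.** Rates of 35%, 25%, 15% and 5%, 80% power, alpha 0.05, 250 per group, 10% dropout and 275 per group all come from Sample size calculations. Equal allocation comes from Randomization and patient allocation ("will be used to allocate patients in a 1:1:1:1 ratio"). The two-sided test comes from Data analysis ("A *P* value < 0.05 with a two-tailed test will be considered significant"). The article does not say which formula or which pair of groups gave 250, so I tried the usual variants.

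**Reproducing 250.** Pooled-variance formula for two proportions:

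n = [z₀.₉₇₅·√(2p̄(1−p̄)) + z₀.₈₀·√(p₁(1−p₁)+p₂(1−p₂))]² / (p₁−p₂)²

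For 25% versus 15%, p̄ = 0.20:

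n = [1.960·√0.32 + 0.842·√0.315]² / 0.01 = (1.1087 + 0.4724)² / 0.01 = 249.98, so 250.

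This matches the plan exactly. The other variants do not:

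| Comparison | Pooled | Unpooled | Continuity-corrected |
|---|---|---|---|
| 35% vs 25% | 329 | 326 | 349 |
| 25% vs 15% | **250** | 248 | 270 |
| 15% vs 5% | 141 | 138 | 160 |

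**The dropout step.**

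- What the plan did: 250 × 1.10 = 275.
- What 10% loss leaves: 275 × 0.90 = 247.5, which is 2.5 below 250.
- What 275 covers: 25/275 = 9.1% loss.
- What 10% loss requires: 250/0.90 = 277.8, so 278 per group and 4 × 278 = 1112 in total. Check: 278 × 0.90 = 250.2.
- Difference from the plan: 3 women per group, 12 in total, or 12/1100 = 1.1%.

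**Effect on power** (pooled formula, two-sided 0.05):

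power = Φ{[(p₁−p₂)·√n − 1.960·√(2p̄(1−p̄))] / √(p₁(1−p₁)+p₂(1−p₂))}

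For 25% versus 15% at n = 247.5: (1.5732 − 1.1087)/0.5612 = 0.828, and Φ(0.828) = 0.796.

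| Per group | 35% vs 25% | 25% vs 15% | 15% vs 5% |
|---|---|---|---|
| 247.5 | 68.1% | 79.6% | 96.2% |
| 250 | 68.5% | 80.0% | 96.3% |
| 275 | 72.7% | 83.6% | 97.6% |
| 278 | 73.1% | 84.0% | 97.7% |

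With the unpooled formula, power for 25% versus 15% at 247.5 is Φ(0.1·√247.5/√0.315 − 1.960) = Φ(0.843) = 80.04%.

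**Bounds.** The row for 247.5 applies if the lost women contribute nothing. The row for 275 applies if imputation recovered everything. Under the plan's 10% dropout, the effective size lies between the two.

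**The case against.** The strongest reply is that the primary analysis is by intention to treat with dropouts imputed, so the denominator is the 275 women randomized and nobody is lost. Part of this stands: 79.6% is a complete-case figure, and the plan does not name complete cases as its primary analysis. But imputation does not supply full information on women whose live birth outcome was never observed, and the plan treats dropout as a loss by inflating for it at all. If nothing were lost, no allowance would be needed. The sentence is inexact on either view.

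A second reply is that the result depends on the formula. That is correct: under the unpooled formula 80% is just held at 247.5. A third is that 9.1% and 10% cannot be told apart as planning guesses, and that the sentence can be read as a plain 10% increase. That is fair as to consequence. It does not make 275 the number that gives 250 after a 10% loss.

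A reader might infer two stronger things. One is that the slip leaves the trial short of 80% power. For 25% versus 15% the documents do not support this: the value is 79.6% or 80.0% by formula with complete cases, and higher to the extent that imputation recovers information. The other is that the slip explains the low power for 35% versus 25%. It does not: that power is 68.5% at the full 250 and only 73.1% with all 278 contributing.

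**Conclusion.** The arithmetic slip is certain and its effect is minor. The stated 275 does not deliver the stated 250 after 10% dropout; it is 2.5 women per group short. For 25% versus 15% the cost is at most 0.4 percentage points of power (80.0% to 79.6%, pooled), and the plausible range is 79.6% to 83.6%, depending on how much imputation recovers. This rests on the assumption that 250 came from 25% versus 15% with the pooled formula, which the article does not state but which reproduces the figure exactly.

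The failure to reach 80% for 35% versus 25% is real and conflicts with the stated power. It arises because 250 matches 25% versus 15%, whereas 35% versus 25% needs 329 by the same formula. It is a separate matter from the dropout step and should not be counted as part of this one. Nothing here calls for more recruitment on account of the dropout arithmetic.

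**What to change.** Keep 1100 women. In Sample size calculations, reword the allowance in one of two ways: 275 per group allows for about 9% dropout, or 10% dropout leaves about 247 per group with observed outcomes. In the same sentence, give power for each hypothesized gap as a range from 247.5 to 275 per group:

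- 35% versus 25%: about 68–73%
- 25% versus 15%: about 80–84%
- 15% versus 5%: about 96–98%

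State that the lower end assumes complete cases only and the upper end assumes that imputation makes every randomized woman fully informative. Add that 250 corresponds to 25% versus 15%, so that the lower power for 35% versus 25% is not put down to dropout.

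The cost is about two sentences of wording. It needs no extra patients and no change to design or analysis. The reported power for 35% versus 25% becomes visibly lower than the 80% now claimed.

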### Data analysis

The primary analysis will use an intention-to-treat approach to examine differences in the live birth rate among the four treatment groups. Primary efficacy analysis will be performed by comparing the treatment groups with respect to the primary outcome of live birth using the Pearson chi-square test. For the secondary supportive analysis, we will fit a logistic regression model to compare the treatment arms with respect to the primary outcome of live birth, adjusting for other factors such as randomization stratification of study site and prior exposure to study medications. Comparisons of variables such as live birth rate, ovulation rate, conception rate, pregnancy rate, multiple pregnancy rate, and miscarriage rate will include relative risk and 95% confidence intervals in addition to the chi-square test. Changes in laboratory values will be assessed by analysis of covariance (ANCOVA).

The analysis of secondary (supplemental) outcomes measured over time will entail the application of statistical methods that have been developed for correlated data because repeated observations will be made over time for each individual. For secondary outcomes such as hormone levels, a linear mixed-effect model will be fit where the main independent variables will be treatment group, time, and their interaction as well as the designed randomization stratification factors as covariates. Logistic regression models will be used in secondary analyses to evaluate the predictive value of treatment arm, clinical site, body mass index, and other explanatory variables on binary outcomes (e.g., live birth, abortion). Cox proportional hazards models and the Kaplan-Meier method will be used to compare time to pregnancy in the treatment groups. Effects on QOL, as determined by the change from baseline physical and mental component scores, will be analyzed by univariate and multivariate ANCOVA. The adequacy of blinding will be tested by Fisher’s exact test comparing true group assignments with participant guesses, including “don’t know.” In order to evaluate acupuncture as a unique therapy, the combination of the personalized acupuncture group and fixed acupuncture group will also be compared with the combination of the letrozole and placebo letrozole groups for the analysis of primary outcome. Differences in AE rates will be analyzed in a negative binomial generalized linear model. A *P* value < 0.05 with a two-tailed test will be considered significant. All statistical analyses will be performed using IBM SPSS Statistics version 21.0 software (IBM Corp., Armonk, NY, USA).

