### Recruitment

A total of 1100 infertile women with PCOS will be recruited from 28 hospitals in China and will be randomly allocated to the following four groups: personalized acupuncture, fixed acupuncture, letrozole, or placebo letrozole. The women will be recruited through advertisements in local newspapers and bulletin boards in each trial center. Prior to participation, eligible women will sign the consent form after a detailed explanation of the study design and comprehensive counseling.

Inclusion criteria are as follows:
Age between 20 and 40 yearsChronic oligomenorrhea or amenorrhea. *Oligomenorrhea* is defined as an intermenstrual interval > 35 days or < 8 menstrual bleedings in the past year. Amenorrhea is defined as an intermenstrual interval > 90 days.Hyperandrogenism (either hirsutism or hyperandrogenemia) or polycystic ovaries on ultrasound. Hirsutism is determined by a modified Ferriman-Gallwey (FG) score ≥ 5 at screening examination [23], and biochemical hyperandrogenism is defined as total testosterone (T) > 2.6 nmol/L and free T ≥ 6.0 pg/ml [24]. (The cutoff level might differ for each study site.) Polycystic ovaries are considered present when the number of small antral follicles (2–9 mm in diameter) is ≥ 12 or the ovarian volume is > 10 ml on transvaginal ultrasound [25].At least one patent tube shown by hysterosalpingogram, contrast sonography, or diagnostic laparoscopy within 3 years if the patient does not have a history of abortion or pelvic operation. If the patient has a history of pregnancy and no history of pelvic operation within the past 5 years, she will not be required to undergo a tubal patency test.Sperm concentration ≥ 15 × 10^6^/ml and total motility ≥ 40% or a total motile sperm count ≥ 9 million in the semen analysis of the husband [26].The couple agrees to have regular intercourse (i.e., two or three times per week) during the study period.

Exclusion criteria are as follows:
Other endocrine disorders:

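### The primary live-birth test and its relative-risk interval leave out study site, although the analysis text treats site as a randomization stratum; if hospitals differ, the crude test is conservative and forgoes some power

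*Protocol article*

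**What the plan says.** All of the analysis statements are in the Data analysis section of the protocol article.

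- The primary efficacy analysis of live birth is described as "comparing the treatment groups with respect to the primary outcome of live birth using the Pearson chi-square test". No strata or covariates are attached to it.
- Live birth and the other rates "will include relative risk and 95% confidence intervals in addition to the chi-square test". Again no strata are named.
- Site appears in the supportive logistic regression of live birth, "adjusting for other factors such as randomization stratification of study site and prior exposure to study medications".
- The mixed model for outcomes such as hormone levels has treatment, time and their interaction, "as well as the designed randomization stratification factors as covariates".

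The Randomization and patient allocation section says only that the web system "will be used to allocate patients in a 1:1:1:1 ratio" and mentions no strata. That randomization was stratified by site is therefore known only from the analysis text. That text also leaves open whether prior exposure to study medication was a stratum or just a covariate.

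**The concern.** Stratified allocation balances the arms within each hospital, so differences between hospitals drop out of the treatment contrast. A crude chi-square still counts those differences as random error. Its variance is then too large, its actual size is below 5%, and its intervals are wider than they need to be. The plan carries the strata into the model for hormone levels but not into the primary test of live birth.

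Two things are at stake: some power on the primary question, and having a crude primary result beside a site-adjusted supportive result that may fall on the other side of P = 0.05. The size of the effect depends entirely on how much hospitals differ.

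**Working it through.** **Inputs from the protocol.** Recruitment: "A total of 1100 infertile women with PCOS will be recruited from 28 hospitals in China". That is 1100/28 = 39.3 women per site, or about 10 per arm per site. Sample size calculations: "Assuming a 35% live birth rate with letrozole, a 25% live birth rate with personalized acupuncture, a 15% live birth rate with fixed acupuncture", and "a 5% live birth rate with placebo letrozole"; 80% power, significance level 0.05, 250 per group raised to 275 for dropout. Data analysis: two-tailed testing.

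**Step 1: reproduce the stated 250.** For an unadjusted two-proportion test with pooled variance under the null,

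n = [1.960·√(2·p̄·(1−p̄)) + 0.8416·√(p₁(1−p₁) + p₂(1−p₂))]² / (p₁−p₂)²

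- 25% vs 15%: (1.960·√0.32 + 0.8416·√0.315)² / 0.01 = (1.1087 + 0.4724)² / 0.01 = 249.98, so 250. This matches the protocol exactly.
- 35% vs 25%: (1.2702 + 0.5422)² / 0.01 = 328.5, so 329. With 250 per group the power is 68.5%.
- 15% vs 5%: (0.8315 + 0.3521)² / 0.01 = 140.1, so 141. With 250 per group the power is 96.3%.

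The planned number was therefore worked out for the same kind of crude test that the plan makes primary.

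**Step 2: size of the crude test, in closed form.** Let τ² be the variance of the true live-birth rate across sites. With arms balanced within site and no treatment effect, the true variance of the difference is a fraction r = 1 − τ²/[p̄(1−p̄)] of what the Pearson test assumes. Its size is 2[1 − Φ(1.96/√r)]. Take p̄ = 25%, so p̄(1−p̄) = 0.1875, with normal site effects on the log-odds scale:

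- SD 0.3: τ² = 0.0031, r = 0.984, size 4.8%. The middle 95% of sites would have rates from about 15% to 37%.
- SD 0.5: τ² = 0.0083, r = 0.956, size 4.5%. Sites from about 10% to 46%.
- SD 0.8: τ² = 0.0192, r = 0.898, size 3.9%. Sites from about 6% to 58%.
- SD 1.0: τ² = 0.0276, r = 0.853, size 3.4%. Sites from about 4% to 66%.

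Interval width was not simulated. By the same ratio, an interval ignoring site would be about 1/√0.956 = 1.02 times as wide as needed at SD 0.5, and 1/√0.853 = 1.08 times at SD 1.0.

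**Step 3: power by simulation.** 40,000 trials per setting, 28 sites of near-equal size, 250 per arm, arms balanced within site, marginal rates held at the protocol's values. Each cell shows Pearson / site-stratified Cochran-Mantel-Haenszel (CMH), in percent.

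| Site SD (assumed) | Power, 35 vs 25 | Power, 25 vs 15 | Power, 15 vs 5 | Size at a common 25% |
|---|---|---|---|---|
| 0 | 68.4 / 68.5 | 80.0 / 80.0 | 96.9 / 96.9 | 5.0 / 4.9 |
| 0.3 | 68.3 / 68.9 | 80.5 / 80.8 | 97.0 / 97.1 | 4.9 / 5.1 |
| 0.5 | 68.9 / 70.6 | 80.8 / 81.7 | 97.1 / 97.2 | 4.3 / 4.7 |
| 0.8 | 69.5 / 73.5 | 81.2 / 83.5 | 97.1 / 97.4 | 4.0 / 5.1 |
| 1.0 | 70.1 / 75.7 | 81.6 / 84.9 | 97.1 / 97.6 | 3.4 / 5.0 |

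The simulated sizes agree with the closed form to within simulation error. Unequal site sizes give nearly the same results: at SD 1.0 the crude size is 3.6%, and the power gaps for 35 vs 25 and 25 vs 15 are 5.5 and 3.4 points.

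**The case against.** The plan can be defended on several grounds.

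- The Pearson test is simple and valid, and it errs only on the conservative side. This stands.
- A site-adjusted model of live birth is already prespecified, so the adjusted answer will be reported. This also stands; the issue is only which analysis is primary.
- The 250 per group was computed for a crude test, so the test and the sample size agree. This stands: Pearson power for 25% vs 15% is 80.0% to 81.6% at every SD examined. The loss is relative to a better test, not to the plan.
- No between-site variation is given, and the larger losses need SDs of 0.8 to 1.0, which nothing in the protocol supports. This stands; at SD 0.5 or less the loss is under 2 points.
- The randomization section names no strata, and this is a condensed article. This is a fair caution, but the analysis text speaks of designed stratification factors and names site.
- With about 10 women per arm per site and a 5% placebo rate, many site cells will have no births. This does not count against the remedy: CMH sums over strata, and a site with no births adds nothing to the test statistic or its variance.

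**Conclusion.** The point holds as a conditional loss of efficiency. If hospitals differ in live-birth rate, the crude primary test runs below its nominal 5% (down to about 3.5% at SD 1.0) and forgoes 0 to about 5.6 power points for letrozole vs personalized acupuncture, 0 to about 3.4 for personalized vs fixed acupuncture, and at most about 0.5 for fixed acupuncture vs placebo letrozole. If hospitals do not differ, nothing is lost.

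The figures assume 250 evaluable women per arm, normal site effects on the log-odds scale, and allocation balanced within site. If allocation was in fact not stratified, the crude test would keep its 5% size and that part of the point would fall away.

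A reader might infer three stronger things that the protocol does not support. First, that the primary analysis is invalid or inflates false positives: the error runs the other way. Second, that power will certainly be lost: this depends on between-site variation that the protocol does not report. Third, that ignoring site is why letrozole vs personalized acupuncture is underpowered. That shortfall (329 needed against 250 planned) is a separate matter, and stratifying does not cure it: CMH reaches only 75.7% even at SD 1.0.

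**What to change.** Before unblinding, make the primary live-birth test for the planned contrasts the CMH test stratified by the actual randomization strata: site, plus prior exposure only if it was a stratum. If a single four-group test is kept, use the generalized CMH test. Report the Mantel-Haenszel relative risk and risk difference with 95% confidence intervals. Keep the crude Pearson test as a sensitivity analysis, and leave the adjusted logistic model as supportive. State the strata in the randomization section so that the two sections agree.

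The cost is wording. Site is already recorded, no additional women are needed, and at SD 0 the stratified test gives up nothing (68.5% vs 68.4% for 35% vs 25%). The one practical check is that the software named in the plan can produce the Mantel-Haenszel relative risk, the risk difference and, if needed, the generalized test; otherwise a second package should be named.

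### The supplementary pooled comparison meant to evaluate acupuncture uses a comparator that averages an active drug with placebo, so it measures acupuncture against neither

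*Protocol article*

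**What the plan says.** The Data analysis section of the protocol article makes the primary analysis an intention-to-treat Pearson chi-square test of live birth across the four groups. It supports this with a logistic model, and with relative risks and 95% confidence intervals for live birth and other rates. Later in the section comes a further comparison, whose stated purpose is to evaluate acupuncture as a therapy of its own: the two acupuncture groups combined "will also be compared with the combination of the letrozole and placebo letrozole groups for the analysis of primary outcome". The general criterion follows in the same paragraph: a P "value < 0.05 with a two-tailed test will be considered significant".

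The planning rates are in Sample size calculations: "Assuming a 35% live birth rate with letrozole, a 25% live birth rate with personalized acupuncture, a 15% live birth rate with fixed acupuncture", and "a 5% live birth rate with placebo letrozole", with "an 80% power at a significance level of 0.05". The article gives no expected effect or power for the pooled contrast, and no reason for joining letrozole with placebo letrozole.

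**The concern.** The pooled pill group joins the arm the trial expects to do best with the arm it expects to do worst. The Background section calls letrozole first-line therapy; the placebo pill is inert. Their average describes no treatment that a woman could receive. A comparison with it moves with the letrozole and placebo rates as much as with the acupuncture rates.

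What is at stake is interpretation. If every planning assumption is right, the expected result is no difference, which could be reported as acupuncture performing like drug treatment. If the drug underperforms, the result can favour acupuncture for a reason unrelated to acupuncture. The choice also sits badly with the Background, which says the evidence is insufficient because no study of live birth used placebo or no intervention as the comparator. This trial has a placebo arm, yet the one analysis devoted to acupuncture as a whole merges it with letrozole.

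**Working it through.** **Inputs.** Live birth rates from Sample size calculations: letrozole 35%, personalized acupuncture 25%, fixed acupuncture 15%, placebo letrozole 5%. Size per group: 250 before and 275 after the dropout allowance (same section). Allocation 1:1:1:1 (Randomization and patient allocation), so each pool is the simple mean of its two arms. Two-sided 0.05 (Data analysis).

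**The plan's own figure.** With n = [1.96·√(2·p̄·(1−p̄)) + 0.842·√(p1(1−p1) + p2(1−p2))]² / (p1−p2)² and 25% against 15%: [1.96·√0.32 + 0.842·√0.315]² / 0.01 = 250 per group, as stated. The plan gives no figure for the pooled contrast.

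**Expected pooled difference.**
- Acupuncture pool: (25 + 15)/2 = 20%.
- Pill pool: (35 + 5)/2 = 20%.
- Difference 0 points, relative risk 1.00.

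**Rejection rate on those rates, 500 against 500.**
- Standard error used by the chi-square test: √(0.20·0.80·2/500) = 0.0253.
- True standard error, since each pool is a fixed mix of two rates: √[(0.1875 + 0.1275 + 0.2275 + 0.0475)/(4·250)] = √0.00059 = 0.0243.
- Rejection = 2·[1 − Φ(1.96·0.0253/0.0243)] = 2·[1 − Φ(2.04)] = 4.1%.
- Simulation (400,000 trials) gives 4.1% to 4.2%, at 250 and at 275 per arm. This is slightly below the nominal 5% because the test overstates the variance.

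**Behaviour at other rates (250 per arm; other rates as planned).**

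| Scenario | Expected difference (acupuncture − pills) | Chance of significance |
|---|---|---|
| Both acupuncture arms 5%, equal to placebo | 5 − 20 = −15 points | near 100%, against acupuncture |
| Both acupuncture arms 35%, equal to letrozole | 35 − 20 = +15 points | near 100%, for acupuncture |
| Letrozole 30% | 20 − 17.5 = +2.5 points | about 16% for acupuncture |
| Letrozole 25% | 20 − 15 = +5 points | about 55% for acupuncture (59% at 275) |
| Letrozole 20% | 20 − 12.5 = +7.5 points | about 90% for acupuncture |
| Placebo 15% | 20 − 25 = −5 points | about 47% against acupuncture (51% at 275) |
| Cited historical rates (letrozole 36.3%, fixed 13.9%) | 19.45 − 20.65 = −1.2 points | about 7% |

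In the first row an inert treatment looks harmful. In the second, one that merely equals the drug looks superior. In the three letrozole rows and the placebo row the acupuncture rates do not change at all.

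**The same data with the comparator split.** Power = Φ[(|d| − 1.96·SE0)/SE1], with 500 acupuncture against 250 in the other group.
- Against placebo (20% vs 5%): SE0 = √(0.15·0.85·(1/500 + 1/250)) = 0.0277; SE1 = √(0.20·0.80/500 + 0.05·0.95/250) = 0.0226; power = Φ(4.24), above 99.9%.
- Against letrozole (20% vs 35%): SE0 = √(0.25·0.75·(1/500 + 1/250)) = 0.0335; SE1 = √(0.20·0.80/500 + 0.35·0.65/250) = 0.0351; power = Φ(2.40) = 99.2% (99.5% at 275 per arm).

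**The case against.** The strongest defence is that little depends on this contrast. It is one added sentence. None of the four objectives uses it, the sample size does not rest on it, and the primary test is the four-group chi-square. The Objectives section states adjacent-arm hypotheses on live birth, and Data analysis provides relative risks and intervals for live birth comparisons. At the planned rates with 250 per arm, fixed acupuncture against placebo (15% vs 5%) has 96% power and personalized against placebo (25% vs 5%) above 99.9%. A misleading pooled result would probably sit beside informative arm-level ones. All of this stands and limits the severity. It does not repair the contrast: the article does not list every pair, and this is the only analysis that evaluates acupuncture as a whole.

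It is also fair to say that the exact zero belongs to the chosen planning rates; the historical rates that the plan cites give −1.2 points. The mixed comparator, however, is a defect at any rates.

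A reader might infer that any shortfall in letrozole makes the test significant for acupuncture. The figures do not support that: at 30% it happens in only about 16% of trials, and it becomes likely only with a large shortfall.

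**Conclusion.** The concern holds for a supplementary analysis. The pooled contrast cannot serve its stated purpose, because neither a null nor a significant result, in either direction, shows how acupuncture compares with placebo or with letrozole. On the planned rates and equal allocation the expected difference is zero and the rejection rate about 4%, while differences of 15 points in opposite directions are hidden. The table's other figures are conditional on the alternative rates shown, which are assumptions except for the cited historical pair.

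A reader might go further and conclude that the trial's primary conclusion is compromised. The document does not support that: the four-group test, the stated objectives and the sample size are all independent of this contrast. The sentence should be corrected, but it is not a fatal flaw.

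**What to change.** Replace the sentence with two contrasts on live birth, both labelled supplementary: (a) pooled acupuncture against placebo letrozole, and (b) pooled acupuncture against letrozole. Report each with the relative risk and 95% confidence interval that the section already provides for.

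State how (a) is to be read. The Blinding section blinds participants only between the two pills, and women given acupuncture know that they receive it, over as many as 48 sessions, some with moxibustion. Contrast (a) therefore estimates the effect of the unblinded acupuncture package against a placebo pill. It should not be described as showing whether needling itself works.

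The cost is one sentence, with no extra patients or data. The small downside is two supplementary tests in place of one, which the label should make plain. The change should be made before unblinding.
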